#### Retention

To promote participant retention and complete follow-up, the project team send out season’s greetings/birthday cards and a small gift (<A$10) to all participants; and follow participants to a nursing home to complete assessments if required. To accommodate for client hospitalisations for less than 2 months during the intervention period, the research team employ ‘stop the clock’ on the intervention until the client is back home or start over and re-do baseline when they get home as their cognitive and physical status may have changed post-hospitalisation. There is a possibility that due to cognitive decline clients will have dementia symptoms consistent with GDRS level 6 at this time. In these cases the clients would still continue their participation in the study because the intention to treat was present at time of enrolment. Decisions as to how many hospital readmissions, and ‘stop the clock’, are allowed per client will be determined on a case by case basis, through consultations with the trial investigators.

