### Methods: study sites, participants, intervention, outcomes and randomisation

#### Sites and sample size

We are recruiting participants across three public hospitals (two of the hospitals are combined into one research site as they have a common geriatric service) and two community aged care providers in the Sydney metropolitan area, New South Wales, Australia. A sample of 128 dyads will give 80% power at the 2-sided 5% significance level to detect a medium effect size of 0.5 between control and intervention groups on the primary outcome assessed at Time 2 (20 weeks, short term effect) and Time 3 (52 weeks, longer term effect). An effect size of 0.5 is clinically relevant as it implies that a trained observer can detect a difference between a control and intervention group in a specified outcome [37], in our case functional independence using the Disability Assessment for Dementia (DAD). We are confident that it is achievable as our pilot study showed a larger effect size of 0.61, as did a similar study of CAPABLE [21]. To allow for 25% loss to follow-up, 170 eligible dyads will be recruited. Based on consultations with the research site partner organisations, we estimated over 500 clients would be potentially eligible for I-HARP from the 4 research sites over 6 months, and a 35% participation rate (based on our previous community trials) would provide 175 dyads. However, current recruitment rates suggest an extra 12 months will be needed to meet the target sample size.

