#### Assessment

There are three assessments: Baseline/Time 1, prior to intervention; Time 2, 20 weeks post baseline; and Time 3, 52 weeks post baseline. All assessments are being conducted by an experienced clinician blinded to group allocation.

*Baseline measures* include socio-demographic data (age, sex, ethnicity, pension status, health insurance, education) and clinical data (health and cognitive conditions, medications). The Addenbrooke’s Cognitive Examination Third edition (ACE-III) [38] and the GDRS [2] are being used to record cognitive function and dementia severity. Following baseline assessment, participants are randomised to either the intervention or the control group.

*Outcome measures* consist of primary and secondary outcomes. The primary outcome is the client’s functional independence at Time 2, assessed using the Disability Assessment for Dementia (DAD) [1] which measures self-care disability and independent living skills. Secondary outcomes are: self-care disability and independence at Time 3; both short- and long-term effects on mobility and physical function, health-related quality of life, carer burden, carer quality of life, and home environmental safety; and total health care costs over the 52 weeks following randomisation. The secondary outcome measures are:Short Physical Performance Battery (SPPB) [39] for objective physical functionCollateral Source version of the Geriatric Depression Scale-15 item (CS-GDS-15) [40] for depressionQuality of life in Alzheimer’s disease (QOL-AD) [41, 42] for general quality of life5-Level version of the EuroQol five dimensions (EQ-5D-5 L) [43, 44] for health-related quality of life (both client and carer) for the economic evaluation, using the Australian weighting algorithm [45]Zarit Burden Inventory (ZBI) [46] for carer burdenThe Home Safety Self-Assessment Tool (HSSAT) for the overall home environment safety.

In addition, monthly telephone contact is made with all carers to monitor participants’ use of prescribed medicines and costs associated, healthcare and community services (type, duration and frequency, and personal costs), incidents of falls and minor injuries as well as carers’ workforce participation (i.e. total number of work hours in the last week). To ensure accurate recording, carers are given a diary/log to complete and during the monthly phone call this is verified. This method was used successfully in the I-HARP pilot.

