#### Randomisation, allocation concealment, and blinding

After recruitment to the study and collection of baseline data (Time 1), each participant is randomly allocated (1:1) to either the intervention or control arm. Randomisation is performed separately for each site and stratified by severity of dementia (mild vs. moderate). Randomisation is performed by computer-generated random permuted blocks of varying size provided by [name] [47]. Opaque sequentially numbered envelopes are used to ensure allocation concealment. Participants are not blinded to group allocation, but assessors and statisticians are. Participants are notified by phone and the importance of blinding is explained. Ethics principles are applied to ensure that participants are supported in this process and understand the blinding processes and potential consequences. The members of the research team responsible for data collection from people with dementia and carers, data entry and analysis will remain blind until completion of the main analysis. Unblinding is permissible for the person who is collecting a monthly carer diary as it may contain information about I-HARP service. This will not contaminate the data to be collected as the information is supplied by the carer.

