#### Data analysis plan

Each indicator of the implementation outcomes will be analysed using descriptive and inferential statistics as well as qualitative content analysis. All analyses of RCT outcomes will be by intention-to-treat (i.e. including all participants, as randomised, regardless of protocol adherence). The primary analysis of the primary outcome (using the DAD) and secondary outcomes will be an unadjusted comparison between intervention and control groups at Time 2 (short-term effect) and Time 3 (longer-term effect) using two sample t-tests of the change from baseline, or Mann-Whitney tests for outcomes that are not normally distributed. Secondary analyses will use linear regression to adjust for the baseline value of that outcome, stratification variables (site and severity of cognitive impairment) and other covariates (age and pension status).

Qualitative field notes and interview data will be fully transcribed and entered into NVivo 11 (qualitative data analysis software package) for analysis. Two-stage data analysis will be conducted: analysis of the field notes and study findings (quantitative data) followed by qualitative content analysis of interviews with research participants (n ≈ 100) and I-HARP interventionists and participating site managers (*n* = 16–24) to explore their perspectives on reablement approaches to care and I-HARP processes, and mechanisms of their decision making.

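### The Retention section lets baseline be re-measured after randomisation, which leaves the change-from-baseline primary outcome open to bias

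*Protocol article*

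**What the plan says.** All references are to the protocol article.

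- **Randomisation, allocation concealment, and blinding:** "After recruitment to the study and collection of baseline data (Time 1), each participant is randomly allocated (1:1"). Baseline therefore precedes allocation. Table 1 agrees: the baseline DAD sits in the enrolment column, ahead of the allocation column.
- **Assessment:** the three visits are "Baseline/Time 1, prior to intervention; Time 2, 20 weeks post baseline; and Time 3, 52 weeks post baseline". Health care costs, by contrast, are counted over 52 weeks from randomisation.
- **Data analysis plan:** the primary comparison is unadjusted, "using two sample t-tests of the change from baseline", with Mann-Whitney tests for non-normal outcomes. The secondary regression adjusts for the baseline value of the outcome.
- **Retention:** for a hospital stay of under two months in the intervention period, the team may stop the clock on the intervention or "start over and re-do baseline when they get home as their cognitive and physical status may have changed post-hospitalisation". How many readmissions and clock stops a client may have "will be determined on a case by case basis, through consultations with the trial investigators". No rule says when to pause and when to start over, or which baseline is then analysed.

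**The concern.** A hospital stay during the intervention period happens after randomisation. A baseline repeated on return home is therefore a post-randomisation measurement, and the stated reason for repeating it is that the client may have changed. If that value replaces Time 1, three things follow:

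- The primary change score no longer starts from a value that randomisation balances.
- The secondary regression does not repair this, because its baseline covariate would be the same post-randomisation value.
- Time 2 and Time 3, dated from baseline, move later for these clients, while the cost window stays fixed to randomisation. Costs and quality-of-life measurements then cover different periods.

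Only the I-HARP arm has an intervention to pause or restart, and nothing parallel is described for controls. If re-baselining happens mainly or only in the I-HARP arm, a hospital-related loss of function drops out of that arm's change scores but stays in the control arm's. A repeat baseline done in one arm only could also reveal allocation to an assessor who is meant to be blinded.

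**Working it through.** **1. The plan's own figures.** The Sites and sample size section states: "A sample of 128 dyads will give 80% power at the 2-sided 5% significance level to detect a medium effect size of 0.5", and "To allow for 25% loss to follow-up, 170 eligible dyads will be recruited".

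- Normal approximation: n per arm = 2 × (1.960 + 0.842)² / 0.5² = 62.8, so 63 per arm, 126 in all.
- Exact t-test with 64 per arm: power 80.1%. The stated 128 is the t-test figure.
- Loss to follow-up: 128 / (1 − 0.25) = 170.7, so 171 against the stated 170.

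These figures reproduce. The check below uses 64 per arm and the design effect of 0.5.

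**2. Order of events.** Time 1 baseline, then allocation, then the intervention period, then (for some) hospital, then a repeat baseline. The repeat falls after allocation, contrary to the Assessment and Randomisation sections.

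**3. Bias formula.** Let h1 and h0 be the shares re-baselined in the I-HARP and control arms. Let D be the hospital-related DAD loss at the repeat baseline, in SD of the change score. Replacing Time 1 by a value lower by D raises that client's change score by D. This is so whether the loss persists (a change of −D becomes 0) or is later recovered (a change of 0 becomes +D). Hence

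bias in the difference of mean changes = (h1 − h0) × D.

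Under the null, the rejection rate comes from the noncentral t with 126 degrees of freedom and noncentrality bias × √(64/2) = bias × 5.657, holding the SD of change at 1.

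**4. One arm only (h0 = 0).** Neither h1 nor D is in the document; both are assumed.

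| h1 | D (SD) | Bias (SD) | Share of 0.5 | Two-sided type I error |
|---|---|---|---|---|
| 5% | 0.25 | 0.0125 | 2.5% | 5.1% |
| 10% | 0.5 | 0.05 | 10% | 5.9% |
| 10% | 1.0 | 0.10 | 20% | 8.7% |
| 20% | 0.5 | 0.10 | 20% | 8.7% |
| 20% | 1.0 | 0.20 | 40% | 20.2% |

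**5. Both arms.** At equal rates, (h1 − h0) × D = 0 and this component cancels under the null. At 15% against 10%, with D from 0.5 to 1.0, it is 0.05 × 0.5 = 0.025 to 0.05 × 1.0 = 0.05 SD.

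**6. The opposite force.** Suppose a fraction f of the I-HARP effect is gained before admission and absorbed into the new baseline. The effect becomes 0.5 × (1 − h1 × f). With h1 = 5% and f = 25% it is 0.494 (power 79.2%). With h1 = 20% and f = 50% it is 0.45 (power 71.4%).

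**7. After the fix.** If Time 1 is the baseline for everyone, both components vanish and the sample size is unchanged.

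**The case against.** The strongest reply is that the document does not say the repeat value is analysed. Assessment equates baseline with Time 1, Table 1 places the baseline DAD before allocation, and a statistical analysis plan could settle which value is used. That stands in part: bias is possible, not demonstrated. It does not remove the point. The Retention section sets out a procedure in terms of re-doing baseline, and nothing says that the original value is kept for analysis. This is a conflict between sections, not a detail left for later.

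Four stronger readings may tempt a reader, and the document does not support them.

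- **Only the I-HARP arm is affected.** This is an inference. It is close to certain for pausing, since controls have nothing to pause. For the repeat baseline it is plausible but unstated: the Retention text speaks of clients, the term the eligibility criteria use for everyone before allocation.
- **The bias must favour I-HARP.** Removing a hospital-related loss from that arm does, but absorbing early benefit works the other way (step 6).
- **Intention-to-treat is breached.** As the Data analysis plan defines it, everyone is analysed in the allocated arm whatever their adherence. The Retention rule excludes nobody and moves nobody between arms.
- **The calendar proves bias.** Four months (17.4 weeks) plus a pause approaching two months (8.7 weeks) runs to about week 26, past the 20-week visit. That concerns pausing, not starting over. Assessment before the programme ends would dilute the effect, not inflate it.

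The objector is also right that equal use in both arms would cancel the main component under the null. Equal use is not assured, however. Hospitalisation is a post-randomisation event that treatment may affect. The plan hypothesises lower health care costs with I-HARP (HP9) and counts hospital costs among them.

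**Conclusion.** Wrong as written. The Retention section permits a post-randomisation baseline, in conflict with the Assessment and Randomisation sections. Followed literally, it carries that value into the primary change score, the secondary regression's covariate and the timing of both follow-up visits.

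The size is conditional. It depends on the repeat value replacing Time 1, on use mainly or only in the I-HARP arm, and on two assumed inputs. Under 5% to 20% re-baselined and a loss of 0.25 to 1.0 SD, the bias is 0.013 to 0.20 SD, or 2.5% to 40% of the design effect, and the type I error is about 5.1% to 20%. The lower end is negligible and the upper end is not. The net direction probably favours I-HARP but is not certain. No figure in the document places the trial within this range.

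**What to change.** Reconcile the Retention, Assessment, Randomisation and Data analysis plan sections by stating three things:

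- The analysis baseline is always the pre-randomisation Time 1 value, in both arms.
- Time 2 and Time 3 are scheduled 20 and 52 weeks from one common origin, randomisation, in both arms, whatever happens to delivery of the intervention. This also aligns them with the cost window.
- A measurement repeated after a hospital stay never replaces Time 1 in any analysis.

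For clients already re-baselined, analyse the original Time 1 value and report their number by arm.

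The cost is a paragraph in the protocol and analysis plan and a visit-window rule in the database. The Time 1 data should already exist, because they are collected before allocation, and the sample size is unchanged. The downside is that some I-HARP clients whose programme was paused will be assessed before finishing it, which slightly dilutes the estimated effect. No view is taken here on how the intervention itself is paused or restarted.

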#### Data consistency and monitoring

Prior to the initiation of the study at any participating centre, all investigators and designated site personnel including I-HARP interventionists and clinical assessors were trained on the study procedures. The training for interventionists and assessors is standardised. Trial monitoring including all matters concerning participant assessments, data collection, intervention delivery, record keeping, and data entry, is performed by the I-HARP data monitoring team on an on-going basis. Accuracy of data entry (100% of the primary outcome measure and 20% of baseline and secondary outcome measure entries) and 100% of the participant consent forms are checked by the data monitoring team. Regular site visits are carried out to ensure that the study is conducted according to ICH-GCP guidelines and as per protocol requirements.

An independent Data Safety and Monitoring Committee (DSMC) was established during Phase I, which meets twice a year to monitor the quality of trial data and the safety of research participants. DSMC membership consists of experts in clinical trial conduct, statistics, aged care and dementia, and terms of reference were determined during the first month of the project. The study is subject to a random audit by the University of Sydney. Any source information and other study files must be accessible at all study sites at the time of auditing and inspection during the course of the study and after the completion of the study.

#### Adverse/serious adverse events

All adverse events and serious adverse events are reported to relevant authorities as per the principles of the *National Health and Medical Research Council Guidance: Safety monitoring and reporting in clinical trials involving therapeutic goods* [49]. This information will also be reported in the annual progress report to the relevant ethics committee and reports to the DSMC.

#### Fidelity

The treatment fidelity plan is based on the CAPABLE Trial Feasibility Strategies [22, 23] which were informed by the NIH Behaviour Change Consortium [50]. The study planning and design has incorporated several steps to ensure fidelity. For example, the site personnel who deliver the intervention have been selected carefully to ensure that they have the necessary qualifications, skills and experience to deliver the intervention to the expected standard. I-HARP clinicians require a minimum 2 years’ experience in the field and person-centred care practice. Group training sessions before the commencement of the study and refresher sessions have been held for I-HARP interventionists from all sites. They have been provided with training manuals and a checklist and trained in assessment tools and intervention techniques. Collection of field notes and case notes is monitored regularly by the project team. The I-HARP checklist, detailed session notes of what has been planned and achieved for each home visit, and 20% of the audio recorded case conferences and home visit sessions are being randomly selected and reviewed by the project team for quality check. The delivery of the interventions and participant compliance with the intervention are also monitored.

Please refer to Table 1: The schedule of enrolment, interventions, and assessments, outlining the timeline of the trial procedures.

**Table 1 Tab1:** The schedule of enrolment, interventions, and assessments

TIMEPOINT^b^	STUDY PERIOD						
	Enrolment	Allocation	Post-allocation				Close-out
	T_1a_ *0 week*	T_1b_ *0 week*	T_2a_ *for 20 weeks*	T_2b_ *at + 20 weeks*	T_3a_ *for 52 weeks*	T_3b_ *at + 52 weeks*	T_4_ *6 months from* T_3b_
ENROLMENT:							
Eligibility screen	X						
Informed consent	X						
Randomisation & Allocation		X					
INTERVENTIONS:							
I-HARP intervention			X		–		
Control: Care as usual			–		–		
ASSESSMENTS:							
*Baseline Variables*							
Global Deterioration Rating Scale (GDRS)	X						
Socio-demographic and basic clinical data	X						
Addenbrooke’s Cognitive Examination (ACE-III)	X			X		X	
*Outcome variables*							
Disability Assessment for Dementia (DAD)	X			X		X	
Short Physical Performance Battery (SPPB)	X			X		X	
Collateral Source version Geriatric Depression Scale (CS-GDS)-15	X			X		X	
Quality of life in Alzheimer’s disease (QOL-AD)	X			X		X	
EuroQol 5 dimensions (EQ-5D-5 L) (client and carer)	X			X		X	
Zarit Burden Interview (ZBI)	X			X		X	
Home Safety Self-Assessment Tool (HSSAT)	X			X		X	
*Other Data Variables*							
Carer diary monthly	X		X	X	X	X	
Interviews with participants				X			
Focus groups with key stakeholders						X	
Adverse/Serious adverse event assessment^a^			X	X	X	X	
Fidelity check	X	X	X	X	X	X	
Reporting of study results^b^							X

^a^Adverse events are monitored and reported as they occur, for the duration of the study

^b^We expect to take about 6 months to complete data analysis and compile the final results paper for an appropriate journal. A summary of the study results will be made available to the referring clinicians and service providers, and study participants

### Dissemination policy

A variety of communication activities will be timed to align with the achievement of key project milestones, targeting different audiences. Key examples are listed below.Producing I-HARP e-newsletters at least twice a year for the promotion and updates of I-HARP among stakeholders (consumers, community groups, service providers);Forwarding of newsletters to promote I-HARP through dementia and aged care related media including Australian Ageing Agenda, Talking Aged Care, Dementia Australia and *Primary Health Network and aged care peak body newsletters;*Peer reviewed publications reporting study results, editorials and letters to the editor; andShowcasing I-HARP on the Aged Care Channel and presentations at local and international conferences and webinars, as well as consumer seminars and events.

I-HARP participants will be provided with a three-page summary of the study findings at the conclusion of the study. Authorship for peer reviewed publications will be based on the International Committee of Medical Journal Editors Guidelines and Recommendations. http://www.icmje.org/

## Discussion

A major gap exists in Australia and internationally in providing care to support and maintain functional and social independence of older people with dementia living at home. Psychological and neurological impairments in people with dementia have negative consequences for their functional and social participation and limit the person’s everyday living and experiences. People with dementia are likely to have difficulties with independently preparing meals, managing finances, making phone calls, shopping, taking medications, dressing, showering and toileting, but critically, they retain the capacity to enjoy a meaningful life with the most appropriate care [51]. In order for people to live well with their dementia, key services and best care practices are needed that recognise and maximise their capacity and capabilities to engage in their daily, physical, social and community activities. I-HARP addresses one of the costliest, often overlooked and significantly undertreated, aspects of old age, particularly among people with dementia: the ability to carry out every-day self-care activities and maintain independence.

Despite mounting evidence concerning reablement approaches to care and the need for interdisciplinary services, no dementia-specific, interdisciplinary reablement model of care has been rigorously trialled in Australia. I-HARP builds on the USA’s CAPABLE study by focusing on people with dementia and working in partnership with family carers. As demonstrated in our pilot, we hope that the key benefits of I-HARP will include the person’s decreased disability in self-care and improved independent living skills, enhanced health-related quality of life, improved functional capacity and confidence in doing activities without falling. It further has potential for reduction in depressive symptoms and care burden, improved carer quality of life and potentially decreased total health care costs in the long term. The I-HARP pilot has also shown that intervention from an interdisciplinary team has the maximum impact. Successful implementation of I-HARP will thus contribute to the following aspects of dementia care and service delivery: early intervention and management; support for people with dementia and their carers in the community that encourages personhood, choice and personalised goal setting.

This project focuses on the implementation and evaluation of I-HARP in existing hospital-based community programs and community aged care settings. The overarching design is a mixed-methods action research approach consisting of a multi-centre, pragmatic, parallel-arm randomised trial, case audits and qualitative methods. During the final phase of the study we will develop future strategies and directions for promotion, dissemination, implementation, and evaluation and sustainability. The research team and Advisory Group will use the information collected on I-HARP performance and processes to make recommendations for improvements and sustainability, and to cite the successes of the I-HARP project. In particular, we will investigate how I-HARP could be incorporated into existing hospital-based geriatric services or home-care programs (Commonwealth Home Support Programs, Home Care Packages, Short Term Restorative Care Program).

This design will allow us to generate evidence for the effectiveness of I-HARP as well as investigate the processes, outcomes and influencing factors of the program implementation to inform consumers, practitioners, service providers and policy makers in their decision making. Implementing a new model of care requires meaningful collaboration between all parties towards change; active engagement and empowerment are two of the most important elements to success. Action research enables this process as it focuses on finding solutions to practical concerns through collaborative, democratic and emancipatory processes [52]. There are four broad rationales for using this evaluation method: 1) to increase accountability, 2) to “steer” the research process, 3) to provide a means for “advocacy”, and 4) to provide an input into the management improvement process (through better understanding and learning). The mixed method action research approach has been used successfully by the investigators in previous studies on models of care and aged care leadership development [53, 54] and found to be effective as it facilitates active involvement of and collaboration between the researchers and key stakeholders in the cycles of change; from project design, problem solving, delivery of research, and planning through to project acceptance and successful implementation, evaluation and translation of project outcomes.

Another strength of the project is co-design of the study with consumers and their involvement throughout the implementation and evaluation processes. Participant consumer involvement is particularly important to the “real-world” significance of this project, as people living with dementia and their carers or family members can surely provide the most relevant insight into real-life problems and needs for this target group. In this project, consumer participants are engaged in two ways:They are invited to join the Advisory Group which will provide a platform for provision of insight and suggestions for people living with dementia and their family/carers. This informs the final planning of I-HARP at Phase I and will contribute to the evaluation of the program. They will participate in the project via a combination of face-to-face meetings, email correspondence and video conferencing to provide their unique perspective on the project’s plan, implementation, dissemination and translation strategies at the individual level.They are involved as research participants, who consistently provide feedback during the face-to-face intervention sessions (as I-HARP interventionists’ field notes form part of the trial’s evaluation methods) and post intervention in-depth interviews (carers), which will provide further opportunity for invaluable comments on the utility of the program for each dyad, with respect to the specific goals of reablement and person-centred care.

Furthermore, establishing broader consumer and community engagement is another important element of implementation evaluation. In order to ensure I-HARP is readily incorporated into the existing home-care programs or hospital-based geriatric services, is scalable and produces optimal outcomes, we are testing I-HARP in the aged care and health care systems – e.g. community aged care services operating under Commonwealth Home Support Programs (CHSP) and Home Care Packages (HCP), and hospital-based community geriatric services, which are designed to support frail community-dwelling older people to maximise their independence in their home environment. As part of the aged care reforms, the Australian government has introduced a number of measures and policies in the provision of care and support for older Australians including changes in CHSP and HCP, and the recently introduced Short Term Restorative Care (STRC) program. Furthermore, with the full implementation of the Consumer Directed Care (CDC) and funding for the CDC packages directly allocated to and following the consumer, patients are given greater control over their choices about not only the home care provider, but also the types of care and services they receive and how those services are delivered. Such contextual information will be taken into consideration in the development of future strategies and directions for promotion, dissemination, implementation, evaluation and sustainability.

I-HARP integrates evidence-based strategies into a dementia-specific person-centred, time-limited, home-based, interdisciplinary rehabilitation package. The project implements and evaluates this novel bio-behavioural-environmental I-HARP model, integrated into existing health and aged care services. The trial will confirm I-HARP’s scalability in community aged care services operating under Commonwealth supported home care service, and hospital-based geriatric services, both of which are designed to support frail community dwelling older people to maximise their independence in their home environment. The Australian government has pledged to deliver “timely, high quality entry-level support services taking into account each person’s individual goals, preferences and choices – and underpinned by a strong emphasis on wellness and reablement” [55] (p.3). Our mixed methods action research approach, combined with a full-scale pragmatic RCT and realist evaluation, will provide a comprehensive picture of the impact, and factors contributing to the outcomes of the intervention, as well as evidence of whether or not I-HARP is cost effective in the real-life context. Such timely insights will provide policy makers and service providers with information relevant to the roll-out of the program in the wider community.

